## Abstract

**Background:**

During hospitalization, many older patients are at nutritional risk or malnourished, and their nutritional condition is often further impaired during hospitalization. After discharge, a “nutrition gap” often occurs in which the patient does not receive enough nutrition to ensure an optimal recovery.

**Methods:**

The study is a randomized controlled study ongoing over 112 days. At discharge, the intervention group receives guidance from a clinical dietitian, and an individualized nutrition plan is made. The dietitian will perform telephone follow-up after 4 and 30 days. It will also be possible for the participant, the participant’s relatives, or the participant’s municipality to contact the dietitian if nutritional questions arise. At the time of discharge, the intervention group will receive a package containing foods and drinks that will cover their nutritional needs on the first day after discharge. They will also receive a goodie bag containing samples of protein-rich, milk-based drinks. Data are collected on quality of life, appetite, physical function, dietary intake, weight, height, energy and protein needs, and experience of discharge and cooperation with the municipality. Information about nutrition status will be sent to the municipality so that the municipality can take over nutritional treatment. The control group receives a standard treatment.

**Discussion:**

This study is the first to combine previously successful single nutritional interventions into a multimodal intervention whose aim is to obtain an effect on patient-related outcomes. We hope that the results will prove beneficial and help to ensure the cross-sector quality of nutritional support to older patients.

**Trial registration:**

ClinicalTrials.gov, NCT03488329. April 5, 2018.

## Background

A multi-international study has shown that, during hospitalization, most older patients are at nutritional risk or malnourished, and their nutritional condition is often further impaired during hospitalization [11]. Malnutrition is directly related to reduced physical function, multiple complications, readmissions, and impaired quality of life [3, 21, 29]. At Herlev Gentofte Hospital, a targeted nutritional effort has been offered to patients at nutritional risk since 2012. The effort consists of a special energy- and dairy protein–enriched food concept consisting of an *a la carte* menu of small dishes enriched with natural energy-dense ingredients and supplemented with a high-quality protein powder and with close follow-up provided by a clinical dietitian. This nutritional effort means that > 85% of the patients with a baseline intake < 50% of the energy and protein requirement achieve ≥ 75% [18]. After discharge, a “nutrition gap” often occurs in which the patient does not receive enough nutrition to ensure an optimal recovery. The lack of nutritional follow-up in connection with older patients’ discharge has a markedly negative effect on functional ability and rehabilitation. This has socioeconomic consequences but also patient-related consequences, such as reduced quality of life and increased dependency on assistance with activities of daily living [15].

According to the recent recommendations of the European Society for Clinical Nutrition and Metabolism (ESPEN), older persons with malnutrition or at risk of malnutrition shall be offered oral nutritional supplements (ONSs) in order to improve dietary intake and body weight and to lower the risk of functional decline after discharge from the hospital [29].

At Herlev Gentofte Hospital and other Danish hospitals, several randomized controlled nutritional intervention studies have aimed at solving the nutritional gap ([1, 2, 6, 9, 14, 24, 25, 27]). These studies have provided individualized dietary counseling, including ONSs if found necessary, but without any provision of food. Even though all these studies have found positive effects on dietary intake and/or nutritional status, the beneficial effect on patient-relevant outcome measures (PROMs), such as quality of life and readmissions, has been very limited ([1, 2, 6, 9, 14, 24, 25, 27]). This is confirmed by systematic reviews conducted in the field [5, 16, 19, 28]. In relation to current national and international guidelines [7, 29], the previous studies may also have been too short in duration to prove beneficial effects on PROMs. In the former studies, the major aim of the dietary counseling has been to improve the intake of energy, and limited focus has been placed on how to optimize the intake of protein to achieve the maximal anabolic response, which seems to be important [12]. In most of the studies, the dietary counseling was provided by dietitians from the hospitals, and only in one study did the municipality play an active role in nutritional support after discharge [27]. Finally, only two of the studies had a focus on dietary intake during the hospital stay [2, 27].

In summary, it appears that in previous studies, single interventions have been examined for a relatively short time and with limited involvement of the municipalities, which may be one explanation for the limited effect on PROMs. The aim of this study is therefore to assess the effect on different PROMs, specifically (re-)admissions, of a long-term multimodal nutritional approach targeted at older patients and involving both hospital and municipality. Our hypothesis is that a more comprehensive intervention study is necessary to elicit a beneficial effect on PROMs.

## Methods

### Study design

The present study protocol describes a 16-week, two-arm, parallel group randomized controlled trial. A planned schedule of enrollment, intervention, and assessment is shown in the Standard Protocol Items: Recommendations for Interventional Trials (SPIRIT) chart in Fig. 1, and items to address in an intervention trial are reflected in Additional file 1: SPIRIT checklist [4]. Flow of the intervention procedure is described in Table 1.

**Fig. 1 Fig1:**
[figure not shown]
Planned schedule for enrollment, intervention, and assessment in Standard Protocol Items: Recommendations for Interventional Trials format. *From the hospital patient register, which is an electronic health record

**Table 1 Tab1:** Multimodal intervention procedure

Intervention group	Baseline, at the hospital	Day 4 after discharge (phone contact)	Day 30 (phone contact)	Day 112
Individualized dietary counseling^a^	x	x	x	x
Individualized nutritional plan^a^	x	x	x	x
Handout nutritional information material^a^	x	X		
Goodie bag^b^	x			
Food package^b^	x			
Communication to municipality^a^	x	(x)	(x)	

^a^Provided by a hospital dietitian

^b^Provided by the hospital kitchen

### Study procedure

#### Recruitment of participants

A sample of 200 (intervention, *n* = 100; control, *n* = 100) patients will be recruited from the oncology, gastrointestinal, and medical departments of Herlev Gentofte Hospital.

##### Inclusion criteria

50+ years of ageIn need of preventive nutritional support or in need of nutritional support due to being at nutritional risk according to the Nutrition Risk Screening 2002 tool [13]Provided with a targeted nutritional effort consisting of a special energy- and dairy protein–enriched food concept (Herlev’s Glories) with close follow-up of a hospital clinical dietitian [17, 18]Discharged to own home (planned)Able to read, hear, and understand the Danish languageCognitively intact (i.e., not diagnosed with dementia or Alzheimer’s disease)

##### Exclusion criteria

Food allergy or intolerancePlanning weight loss or following a special dietReceiving enteral or parenteral nutrition at dischargeModerate to severe dysphagia, defined as a need for a texture-modified dietPermanently bedridden and hence not expected to be discharged to own homeDischarged to nursing home or rehabilitation stayIn droplet infection isolation, because not allowed to bring in weighing scales for baseline data collectionIn late palliative or terminal phase, assessed from 6 months of expected survivalAccelerated and disseminated cancer

There are no restrictions on concomitant care or interventions during the trial, except for those specified in the exclusion criteria.

#### Procedure

Prior to initiation of the study, posters will be developed, and introduction meetings will be held to inform the staff of their role in the recruitment process. Screening and recruitment of study participants will be carried out in collaboration with the departments’ doctors and nurses by the project’s research assistants and research dietitians. The research team will assess interested patients against the eligibility criteria. Individuals deemed eligible and who wish to participate will have their written informed content obtained. Individuals deemed ineligible will have the exclusion criteria recorded. Individuals deemed eligible but who do not want to participate will have their reason for declining recorded and will be asked for permission to use the hospital patient register to collect their baseline and follow-up data recorded there (see Fig. 1).

#### Randomization and blinding

Randomization will take place after each participant has been included in the study, has been assigned an identification code, and has completed the study baseline assessment. The participants will be randomized into two groups: intervention versus control. Before inclusion begins, 28 large, opaque envelopes are created that contain 8 smaller opaque envelopes. The smaller opaque envelopes are sealed and contain a piece of paper stating either “intervention” or “control.” When randomization takes place, the participant selects his or her envelope from the large envelope, thus making it a lottery. When the content of the large envelopes is down to three small envelopes, the small envelopes are transferred to a new large envelope. This is done to prevent situations where the outcome of randomization can be guessed. The large envelopes are kept in a locked cabinet and are only available for the research dietitians and assistants. The hospital dietitians will include participants, and they will gather data at baseline and at 4 and 30 days. A research assistant will collect data at 112 days and 6 months. The research assistant will also oversee data entry. It is not possible to blind involved research assistants, hospital dietitians, and participants, owing to the type of intervention provided. The municipalities will only receive communication regarding the participants in the intervention group and will therefore not know who is in the control group. The statistician will be blind to group allocation until completion of the statistical analysis.

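### The envelope carry-over reduces but does not prevent guessing of the next allocation, and the unblinded staff who recruit also have access to the envelopes

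*Protocol article*

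**What the plan says.** All of the following is in the protocol article.

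- **Set-up** (Randomization and blinding): "28 large, opaque envelopes are created that contain 8 smaller opaque envelopes". Each small envelope is sealed and names one of the two arms. How many of each arm go into a large envelope is not given.
- **Draw** (same section): "the participant selects his or her envelope from the large envelope, thus making it a lottery".
- **Carry-over** (same section): "When the content of the large envelopes is down to three small envelopes, the small envelopes are transferred to a new large envelope". The purpose is given as: "This is done to prevent situations where the outcome of randomization can be guessed".
- **Access** (same section): "The large envelopes are kept in a locked cabinet and are only available for the research dietitians and assistants".
- **Recruitment** (Procedure): screening and recruitment are carried out, with the wards' doctors and nurses, "by the project’s research assistants and research dietitians". The research team also judges eligibility.
- **Blinding** (Randomization and blinding): research assistants, hospital dietitians and participants cannot be blinded.
- **Timing** (same section): a participant is randomized only after inclusion, assignment of a code and completion of the baseline assessment.

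**The concern.** The article claims a property for the carry-over rule, so the rule can be tested against it. Envelopes are drawn without replacement from a small set: eight at first, then three plus eight. Staff who learn each result and know the starting mix can work out what is left. The carry-over avoids drawing from the last three, but any imbalance among those three passes into the next set.

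This matters because the same roles recruit and have access to the envelopes. Someone who expects the next draw to be, say, control can choose whom to approach next, or delay an approach. If that choice is related to prognosis, the arms differ at entry. The register would then record that difference accurately as a difference in admissions.

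**Working it through.** The article gives no figure for predictability, so there is none to reproduce.

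**Inputs from the article.** 28 × 8 = 224 small envelopes; 200 participants, 1:1; transfer when three remain; planned 6-month admission proportions of 28% and 52%, a difference of 24 points.

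**Assumptions.** (a) Each large envelope holds four of each arm. (b) The three left over join the eight in the next large envelope, making 11. (c) Staff know the mix and keep a tally. (d) The guess is always the arm with more envelopes left.

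**Step 1: chance of a correct guess.** With *i* intervention and *c* control envelopes left, the best guess is right with probability max(*i*, *c*)/(*i* + *c*). I averaged this exactly over all possible compositions for 200 draws, adding 4 + 4 whenever three remain.

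| Scheme | Mean correct guess | Correct of 200 | Draws predictable at 2/3 or better | Certain draws per trial |
|---|---|---|---|---|
| Carry-over of three, 4:4 | 60.5% | 121 | 26% | 2.3 |
| Blocks of 8, no carry-over | 66.6% | 133 | 44% | 40 |
| Independent 50:50 allocation | 50% | 100 | 0% | 0 |

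Certainty can arise as early as draw 5. After four draws from the first eight, the four left are all of one arm with probability 2/C(8,4) = 2/70 = 2.9%. At the last draw before each later transfer, certainty occurs about 7% of the time. In simulation, about 81% of trials contain at least one certain draw.

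**Step 2: other values of the unstated inputs.** If 112 + 112 slips were shuffled freely across all 28 envelopes, and staff tallied against that total, the mean correct guess is 52.8% (105.5 of 200). If staff do not know the mix or keep no tally, it moves towards 50%.

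**Step 3: possible bias.** Assume that recruiters can choose between patients whose 6-month admission risks are 50% and 30% (20 points apart), and that they act on the guess in a fraction *f* of draws. With mean correct-guess probability *g*, the spurious difference is about 20 × *f* × (2*g* − 1).

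- 4:4 mix: 2 × 0.605 − 1 = 0.21, so the bias is 4.2 × *f*. This is 1.0 point at *f* = 25%, 2.1 at 50% and 4.2 at 100%. Simulation gives the same values.
- Free shuffle: 2 × 0.528 − 1 = 0.056, so the bias is 1.1 × *f*. This is 0.3, 0.6 and 1.1 points.

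**Step 4: would small varying blocks be better?** I simulated 200 draws with block sizes chosen at random, guessing the arm with fewer allocations so far. The correct-guess rate was 70% for blocks of 2/4/6, 68% for 4/6/8 and 66% for 6/8/10. All are above the 60.5% of the envelope scheme.

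**Step 5: custody.** No arithmetic is needed. The roles named in "The large envelopes are kept in a locked cabinet and are only available for the research dietitians and assistants" are the roles that the Procedure section makes responsible for screening and recruitment.

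**The case against.** Much of the opposing case stands.

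- **The rule does most of its job.** It cuts certain draws from 40 to about 2.3 per trial, and the sentence can be read as aimed only at end-of-envelope certainty. Even so, it speaks of preventing guessing without that limit, and certainty itself is not fully removed.
- **The 60% rests on an unstated mix and a shared tally.** True. The article does not say that staff know the mix or keep count, and several recruiters work across departments. The two mixes examined give about 53% and 60%.
- **Guessing above chance comes with restricted randomization in an unblinded trial.** Also true, and it rules out small varying blocks as a remedy. It does not rescue a claim that guessing is prevented, nor explain why recruiters need access to the envelopes.
- **There are safeguards.** Randomization after inclusion and baseline protects the data of someone already enrolled. Recorded reasons for exclusion and refusal make selective recruitment easier to detect. Neither controls whom staff approach next. Register outcomes and a blinded statistician address assessment and analysis, not selection at entry.

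Three stronger readings are tempting, and the documents support none of them. One is that selection bias occurred: nothing shows that staff guessed or steered. Another is that no one outside the team prepared or held the allocations: the article does not say who prepared the envelopes, and a condensed article's silence is not evidence. The third is that the authors call the primary outcome free of bias: Strengths and limitations says only that register data lower the risk, in a paragraph about lack of blinding.

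**Conclusion.** The point holds in a limited form. The carry-over makes the next allocation harder to guess, but the procedure as printed does not prevent guessing. The best guess is right about 60% of the time with a 4:4 mix and about 53% with a free shuffle, in both cases if staff know the starting numbers and keep a tally. The overlap between those who recruit and those with access to the envelopes rests on the text alone.

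The likely effect on the primary comparison is small: about 1 to 2 points at 25% to 50% steering, under an assumed 20-point risk difference and a 4:4 mix, against a planned 24 points. It is less with a free shuffle. This calls for a correction and one supporting analysis; it does not invalidate the trial.

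**What to change.** Trial status describes recruitment both as ongoing at submission and as completed in October 2019, so both cases are covered.

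**Any remaining enrolment.** Use a computer-generated list, unblocked or with only loose restriction, held outside the recruiting team. Release one allocation at a time after baseline, keeping the timing already planned. Do not use small varying blocks (Step 4). The cost is small. Arm sizes may be modestly unequal: with 200 unblocked allocations, the standard deviation of one arm's size is √(200 × 0.25) = 7.1, so about 95% of trials have between 86 and 114 in that arm.

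**Participants already randomized.**
1. Change *prevent* to *reduce* in the sentence on the carry-over.
2. Report who prepared and held the envelopes, and the mix in each large envelope.
3. Add a sensitivity analysis of the primary outcome adjusted for prognostic variables known at entry, such as cancer diagnosis, department and age.
4. Only if envelope composition and draw order were recorded, reconstruct each participant's allocation probability and test whether baseline risk is associated with it. The article describes no such log, so this may not be possible.

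Items 1 to 3 cost a wording change, two reported facts and one extra model, with no new data collection.

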#### Primary outcome

##### Admissions after 6 months

Nonplanned admissions within 6 months will be assessed using data from the hospital patient register, where the number of admissions can be found. The prevalence in each group will be calculated. The length of stay at each admission is also recorded and averaged for the two groups.

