### Strengths and limitations

A major strength of this study is that we have chosen a longer intervention period than former studies, as also recommended by, for example, ESPEN [29]. This will hopefully increase the chance of finding a positive effect on PROMs.

To our knowledge, this study is the first to combine previously successful single nutritional interventions into a multimodal intervention. A major strength in relation to this is that we have been involved in several of the former single nutritional intervention studies and therefore have detailed information about how these studies were carried out.

Recruitment flow can be difficult when studying older patients at nutritional risk, because they might not be able to overcome participation in the study. Previous studies of older patients have seen a high rate of patients who reject participation. A strength in this study, however, is that we ask participants for permission to collect relevant data from their hospital record in order to investigate if the nonparticipating patients differ significantly from the population receiving the intervention.

Due to the nature of the intervention, it is not possible to blind researchers, dietitians, and participants. However, our primary outcome is risk of admissions, and these data will be collected from the hospital patient register, which will reduce the risk of bias. Furthermore, the statistician will be blinded to group allocation until completion of the statistical analysis, which is also a strength.

One limitation is that we only have close control over the first part of the intervention (i.e., the first 30 days) when the hospital dietitians are involved. Even though the nutritional care plan is communicated to the municipalities and the majority of these have dietitians working with old people, we do not know if these will continue and support the intervention started by the hospital dietitians. Furthermore, we have limited knowledge about the other types of nutritional support available in the municipalities (e.g., energy- and protein-dense meals-on-wheels, nurses in charge of nutrition, availability of the staff to provide support with shopping of recommend foods). Finally, the participants might say “no” to the municipality’s offer. In a former study involving general practitioners, this was an unexpected finding [1].

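### The research assistant who collects the register-based primary outcome is declared impossible to blind, for a reason that does not apply to a register look-up

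*Protocol article*

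**What the plan says.** Three places in the protocol article bear on this.

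- **Randomization and blinding.** On who collects the later data: "A research assistant will collect data at 112 days and 6 months. The research assistant will also oversee data entry". On blinding: "It is not possible to blind involved research assistants, hospital dietitians, and participants, owing to the type of intervention provided". The only role declared blinded to allocation is the statistician: "The statistician will be blind to group allocation until completion of the statistical analysis".
- **Primary outcome.** On the endpoint and its source: "Nonplanned admissions within 6 months will be assessed using data from the hospital patient register, where the number of admissions can be found". Length of stay at each admission is recorded as well.
- **Strengths and limitations.** The lack of blinding is acknowledged and answered with the data source: "our primary outcome is risk of admissions, and these data will be collected from the hospital patient register, which will reduce the risk of bias". The blinded statistician is named as a second safeguard.

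Outcome assessments adds that the assistant who collects data at 16 weeks takes no part in the intervention. It lists register extractions at baseline and at days 4, 30 and 112. Randomization and blinding is the only section that says who collects data at 6 months.

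**The concern.** The plan does not merely leave blinding of the outcome collector unmentioned. It says that blinding is not possible and gives a reason, and that reason covers only part of what the assistants do. Staff who counsel, telephone or visit a participant will learn the arm. Someone who reads admissions from a register against an identifier and a discharge date need not.

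The primary endpoint is restricted to nonplanned admissions, so at some step each admission has to be counted or left out. If a person who knows the arm takes that step, even partly, borderline admissions can be treated differently in the two groups. An outcome file formed in that way passes the error on to the statistician, blinded or not. The endpoint that carries the trial's conclusion would then lack a protection that costs little.

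**Working it through.** **1. Does the stated reason fit the task?** In the text shown, the outcomes reaching to 6 months are admissions, with their length of stay, and mortality. All come from the hospital patient register, and no participant contact at 6 months is described (the schedule figure is not shown). The reason given, the type of intervention, concerns contact with participants, so it does not reach this task.

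**2. Is extraction without the arm feasible?** Each participant receives an identification code before randomization. The Procedure section also plans to take register data, with permission, for eligible patients who decline to take part. Register extraction is thus already foreseen outside any treatment contact.

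**3. Is the collector likely to know the arm?** Probably. Randomization and blinding gives research dietitians and assistants access to the allocation envelopes. Research assistants make the 16-week home visits, at which short counselling may be given in the intervention group and none is given in the control group. The statement that the 16-week collector is not part of the intervention means independence from delivery, not ignorance of allocation.

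**4. Do the two named safeguards cover the gap?** The register protects the record that an admission took place. The blinded statistician protects the analysis. Neither covers the step between them, where admissions are abstracted and sorted.

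**5. Who sorts planned from nonplanned?** The text does not say. It gives no rule for classing an admission as nonplanned, and does not state whether the register holds a code for it.

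**6. How large could the effect be?** The document cannot answer this, so what follows is an illustration.

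The plan's own figure comes first. With 28% against 52%, two-sided alpha read as 0.05, power 0.80 and pooled variance:

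n = [1.960 × √(2 × 0.40 × 0.60) + 0.842 × √(0.28 × 0.72 + 0.52 × 0.48)]² / 0.24² = 64.2

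This is 65 per group when rounded up, against the 64 stated. The unpooled formula gives 62. The stated size is reproduced, and this point does not dispute it.

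Now assume no true effect, with p = 0.52 in both arms and 100 per group. Assume also that a share m of intervention patients with an event is counted as having planned admissions only. Then p₁ = 0.52 × (1 − m) and d = 0.52 − p₁. With p̄ = (p₁ + 0.52)/2, se₀ = √(2p̄(1 − p̄)/n) and se₁ = √([p₁(1 − p₁) + 0.52 × 0.48]/n), the probability of rejection is

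Φ((d − 1.96 se₀)/se₁) + Φ((−d − 1.96 se₀)/se₁).

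| m (assumed) | Intervention arm | Apparent benefit | Rejection, 100 per group | Rejection, 64 per group |
|---|---|---|---|---|
| 0 | 52.0% | 0 | 5.0% | 5.0% |
| 5% | 49.4% | 2.6 points | 6.6% | 6.0% |
| 10% | 46.8% | 5.2 points | 11.4% | 9.0% |
| 20% | 41.6% | 10.4 points | 31.3% | 21.7% |

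The difference used for planning is 52 − 28 = 24 points. If a register code is copied without judgement, m is about zero and the first row applies.

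**The case against.** The strongest case against is that no sentence describes a biased step. A reader might infer that an unblinded assistant personally decides which admissions were planned. The document does not say so: it says that the outcome is assessed from register data. Nor does it say that the assistant enters the data; the assistant oversees entry. If the register codes the admission type, copying the code leaves little room for bias. The authors have also acknowledged the lack of blinding and chosen a register endpoint in response. Coding rules and file handling are details that a journal article may leave to the full protocol.

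Much of this stands. The judgement step is a possibility left open, not a stated fact. The relabelling shares in the table are assumptions, and nothing in the document supports any particular nonzero value. It might be argued that the cancer patients make borderline admissions likely, but the document gives no evidence of that. It also excludes accelerated and disseminated cancer and wants enough power with the cancer patients removed. Nor is the primary outcome the only one that could be collected blind: 30-day and 112-day admissions, length of stay and mortality come from the same register.

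What does not stand is the appeal to condensation. The article makes a positive statement that the assistants who collect outcomes cannot be blinded, and the reason given does not fit register work. That is a choice fixed in the text, not a detail left out.

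**Conclusion.** The point holds as an avoidable risk of bias in the primary outcome, not as a demonstrated bias. The plan assigns the 6-month collection and the oversight of data entry to a role that it declares unblindable, on a ground that does not extend to a register look-up. Its two safeguards leave abstraction and classification uncovered.

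The size cannot be derived from the document. It is about zero if a register code for admission type exists and is copied. Under the assumed relabelling of 5% to 20% in one arm, the spurious benefit is 2.6 to 10.4 points. A reader might take these figures as an estimate, or conclude that the primary result will be biased; the text supports neither. The conclusion rests on two readings: that the 6-month collection by the assistant includes the register outcome, and that the assistants usually know the arm. The change is worth making because it costs little and protects the main endpoint.

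**What to change.** Limit the sentence on blinding to those to whom it applies, and describe the register extraction separately. Suggested text:

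> Participants, and staff at counselling sessions, phone contacts and home visits, cannot be blinded. Admissions, length of stay and mortality at 30 days, 112 days and 6 months are extracted from the hospital patient register against a list of identifiers and discharge dates that does not contain the allocation. Nonplanned status is taken from the register code if one exists; otherwise each admission is classified by a person unaware of the arm, under a rule written beforehand. The outcome file is locked before it is linked to the allocation.

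A data pull is preferable to reading the full record. The register is described as an electronic health record, and the record may reveal the arm. For the same reason the statistician should not be asked to read records, since that could compromise the one blinded role in the plan.

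The cost is a changed order of data handling, with no change to participant contact and no need for extra staff. If a register code is used, the small downside is that admissions are not reviewed case by case. If the 6-month data have already been collected, the extraction could be repeated in this way, or the report should state who classified the admissions and whether they knew the arm.
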